## Abstract

**Background:**

GHB dependence is a growing health problem in several western countries, especially the Netherlands. Attempts to stop using GHB are often followed by relapse shortly after successful detoxification. Craving for GHB use and co-morbid psychiatric symptom levels are thought to be the major factors contributing to the high relapse rates. Given its pharmacological profile, baclofen might prove an effective anti-craving agent for patients with GHB dependence. The aim of the current study is to assess the potential of baclofen as an anti-craving agent relapse prevention intervention in GHB dependent patients.

**Methods/Design:**

In an open label non-randomized trial treatment with baclofen to a maximum of 60 mg/day will be compared with treatment as usual (TAU) in recently detoxified GHB dependent patients (n = 80). The primary outcome measure will be the level of GHB use. Secondary outcome measures are craving levels, psychiatric symptom levels and quality of life. Questionnaires will be administered during 12 weeks of baclofen treatment and at follow-up (six months after the start of treatment).

**Discussion:**

It is hypothesized that baclofen treatment compared to TAU will be associated with significantly reduced GHB use. In addition, we hypothesize that baclofen treatment will be associated with decreased craving and anxiety levels, and higher quality of life. If results are in line with our hypotheses, further studies on the efficacy of baclofen using placebo controlled designs and long term follow-up are warranted.

**Trial registration:**

The Netherlands Trial Register with number NTR4528. Registered 19 April 2014.

## Background

GHB use is a growing public health issue in several Western countries, including the Netherlands [1]. Recreational use of GHB has gained popularity over the past decades [2]. As a result, it’s addictive potential has become more apparent [3]. Little is known about the exact prevalence of chronic GHB dependence in the USA and Europe due to the absence of surveillance and systematic reporting mechanisms [4]. Nevertheless the number of GHB users seeking help increased over the past years [5]. For example, the number of GHB dependent patients admitted in addiction treatment facilities sharply increased in the Netherlands, over the last five years from 60 in 2008 to almost 800 patients in 2013 [6].

Gamma-hydroxybutyrate (GHB) is a short-chain fatty acid that is an endogenous precursor and metabolite of gamma-aminobutyric acid (GABA). GHB administered systemically can cross the blood–brain barrier where it acts both as neurotransmitter and a neuromodulator [7]. It has a plasma half-life of approximately 30–60 minutes [8]. GHB has high affinity for the GABA-B receptor and to a lesser extent for subtypes of the GABA-A receptor [9]. GHB has impact as neuromodulator via both GABA-ergic effects and direct effects on a wide variety of other neurotransmitters, including glutamate, dopamine, serotonin, noradrenaline, acetylcholine, opioids, and GABA [10-12]. GHB has various therapeutic applications, like general anesthesia [13], treatment of sleep disorders as narcolepsy [14], and the treatment of alcohol [15] and opioid withdrawal [16].

GHB tolerance occurs rapidly when used daily, inducing physical dependence at higher doses. Discontinuation of GHB can produce severe withdrawal symptoms as anxiety, delirium with auditory and visual hallucinations, seizers, and coma, which may be life threatening [17,18]. Recent studies have shown safety of strategies for the detoxification in GHB dependence, using tapering with pharmaceutical GHB or benzodiazepines [19]. Nevertheless, high relapse rates hamper long-term recovery, despite psychological treatment and counseling. Forty-five percent of the cases reporting to addiction care facilities had previously been in treatment for GHB dependence [19]. Indeed, short-term relapse rates up to 64% have been reported [20]. Self-reported reasons for relapse include social pressure, craving for and loss of control over GHB use and increased anxiety and depression after stopping GHB use [21].

Here we present a study protocol investigating the potential of baclofen in relapse prevention and its anti-craving properties in recently detoxified GHB dependent patients. Baclofen is a high affinity GABA-B receptor agonist with a half-life ranging from 2 to 6 hours [22]. The pharmacological overlap between baclofen and GHB suggests that the relatively long-acting baclofen may serve as a substitute for the short acting GHB. Moreover, baclofen is thought to modify brain reward function, through its indirect effects on dopamine, which has been suggested to be a key neurotransmitter for craving [23-25]. Finally, baclofen is thought to have anxiolytic effects through its agonist effects on the GABA-B receptor [26]. Overall, it could be speculated that baclofen may be effective in relapse prevention in GHB dependent patients. Indeed, animal data have shown beneficial effects of baclofen on GHB self-administration in mice [27].

### Aims and hypotheses

The primary aim of the current study is to assess the potential of baclofen to prevent relapse in recently detoxified GHB-dependent patients. We hypothesize that administration of baclofen to GHB-dependent patients after detoxification is associated with decreased relapse rates as compared to treatment as usual (without baclofen). We also hypothesize that treatment with baclofen is associated with reduced levels of craving for GHB and reduced psychiatric symptoms levels, including anxiety, and increased quality of life. We expect baclofen treatment to cause minimal side effects in these patients. Finally, we expect a lower drop-out rate from adjuvant therapy (TAU) in the intervention group.

## Methods and Design

### Study design

The design is of an open label non-randomized controlled clinical study in six addiction care facilities in the Netherlands. The study is part of the Dutch national GHB Monitor 2.0 and data collection will take place between May 2014 and December 2015. After successful detoxification of GHB, patients will receive either baclofen on top of treatment as usual (TAU + baclofen) or treatment as usual (TAU) only. Assignment is based on in- and exclusion criteria and on patient preference (informed consent).

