### Participants

#### Recruitment

Participants are GHB dependent patients in treatment for detoxification at six participating addiction care facilities. These GHB dependent patients will be informed by their physician about the possibility to participate in the current study before GHB detoxification. The physician will inform the research nurse per centre on potential participants for the study, who will provide further study information to the patients after the detoxification. After informed consent, a research physician will perform the medical screening. The intervention group will be compared with two control groups: recently detoxified GHB dependent patients included in the Dutch national GHB Monitor 2.0, but that do not want to use baclofen (TAU only); and a matched historical control group from our previous work on GHB dependence (n = 274) of whom follow-up data are available [20]. The historical control group will be matched on age, gender, GHB use (dose and years), and number of detoxification attempts.

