#### In- and exclusion criteria

Patients are eligible to participate if GHB dependence (according to the DSM-IV general criteria of dependence) is their primary diagnosis [28] and their age is at least 18 years. All participants should be able to read and speak the Dutch language. Patients with any current somatic or psychiatric safety concerns are excluded. Exclusion criteria are liver cirrhosis and impaired renal function (as indicated by aspartate aminotransferase (AST)), alanine transaminase (ALT), or gamma-glutamyl transferase ((GGT) level >3 times the upper limit of normal (ULN); bilirubin > ULN; serum creatinine > ULN), unstable hypertension, unstable diabetes mellitus, seizure disorder including patients currently taking anticonvulsants, and pregnancy. Patients experiencing current severe mood disorder (bipolar disorder or major depressive disorder), current psychotic disorder (including schizophrenia), and/or suicidal ideations and patients suffering Parkinson’s disease will be excluded too. Co-current use of anxiolytics, stimulants or hypnotics will not be permitted.

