**Table 2 Tab2:** **Time measurements**

**Week**	**0**	**1**	**2**	**3**	**4**	**5**	**6**	**7**	**8**	**9**	**10**	**11**	**12**	**13**	**14**	**15**	**24**
Measurement	**T0**-baseline	**T1**											**T2**				**T3**
Mate section	xx												xx				x
EQ–5D	xx												xx				x
DASS	xx												xx				x
Mini-plus	xx												xx				x
Blood	xx						x						x				
Urine	xx						x						xx				x
Medical consult	2x	2x	2x	x	x			x			x		x	x	x		
Baclofen (mg)	0	15–30	45– 60											30–45	30–15	15–0	0
Baclofen Side effect	x	2x	2x	x	x			x			x		x				
VAS	xx	x	x	x	x			x			x		xx				x
DDQ	xx	x	x	x	x			x			x		xx				x
Baclofen withdrawal checklist														x	x	x	
Timeline follow back													xx				x

xx = baclofen group and control group TAU only.

x = baclofen group.

T0 = end of GHB detoxification.

T1 = start baclofen treatment.

T2 = follow-up TAU only and end of baclofen therapy.

T3 = follow-up baclofen group.

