## Discussion

This study protocol presents the design of an open label clinical trial evaluating the efficacy of baclofen to prevent relapse, reduce craving and anxiety, and to assess the safety profile of baclofen in GHB dependent patients. To date, there are no reports on the potential of baclofen to prevent relapse in GHB dependent patients. We expect that baclofen will increase abstinence rates, reduce craving and will be well tolerated. In addition, baclofen may improve psychiatric symptoms such as anxiety and depression, as suggested in several clinical trials in alcohol-dependent individuals [29,30,46].

Several risks of baclofen use are taken into account in the current study. In patients with neuropsychiatric disorders, such as schizophrenia, severe depression, mania, Parkinson’s disease and cerebrovascular diseases, exacerbations of these conditions may occur, when the dose of baclofen is rapidly increased. It may lower the threshold for seizures in epileptic patients [42]. To limit these risks in the current trial, baclofen will be uploaded gradually, over a period of minimally 10 days. Moreover, patients previously diagnosed with any of the mentioned diseases will be excluded from the study.

Abrupt discontinuation of baclofen, when used for several months, can be associated with a withdrawal syndrome which resembles benzodiazepine and alcohol withdrawal. Several symptoms are reported such as hallucinations, fever, confusion, delirium, agitation, insomnia, and muscle stiffness and spasms [47]. Therefore, patients will be advised to taper down slowly when discontinuation is needed.

Intoxication with baclofen has been reported in doses above 100 mg [48]. This risk increases if patients combine baclofen with GHB. Intoxication is not expected when baclofen is administered at a low dose (<30 mg per gift), as applied in the current study. Patients will however, be informed repeatedly of this potential risk and the treatment will be discontinued immediately in case of relapse.

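### The protocol defines the TAU-only control group in two incompatible ways; read literally, one of them admits patients who fail the eligibility criteria and so could never be in the baclofen group

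*Protocol article*

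**What the plan says.** Four places in the protocol article bear on who is a concurrent control.

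- **Study design** introduces the two groups and then gives the rule for reaching them: "Assignment is based on in- and exclusion criteria and on patient preference (informed consent". Criteria and preference are named together as the basis of assignment.
- **Recruitment** defines the concurrent controls as "recently detoxified GHB dependent patients included in the Dutch national GHB Monitor 2.0, but that do not want to use baclofen (TAU only". Refusal is the only route given, and failing the criteria is not mentioned.
- **In- and exclusion criteria** treats the criteria as conditions for taking part. It opens the exclusions with a broad clause, "Patients with any current somatic or psychiatric safety concerns are excluded". It then lists liver and renal limits, unstable hypertension and diabetes, seizure disorder, pregnancy and Parkinson's disease, and on the psychiatric side "Patients experiencing current severe mood disorder (bipolar disorder or major depressive disorder), current psychotic disorder (including schizophrenia), and/or suicidal ideations".
- **Discussion**, on the risks of baclofen in neuropsychiatric disease, says that "patients previously diagnosed with any of the mentioned diseases will be excluded from the study".

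On prognosis, the Abstract states: "Craving for GHB use and co-morbid psychiatric symptom levels are thought to be the major factors contributing to the high relapse rates".

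Table 2 marks week-0 blood and MINI-plus with a double cross, and its legend reads "xx = baclofen group and control group TAU only".

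**The concern.** If the criteria help decide the arm, they create a difference between the arms that is separate from patient preference. Preference bias operates among patients who could have been in either group. A patient barred from baclofen by the criteria has no counterpart in the baclofen group, so covariate adjustment has nothing to compare that patient with.

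The main comparison at stake is abstinence at 3 months. Statistical analyses plans a Pearson chi-squared test for it, which carries no covariates. The general covariates named there are socio-demographic, such as age and gender, and do not capture eligibility. With six centres, and an exclusion clause that leaves room for judgement in an open-label study, different sites could also settle the question differently.

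**Working it through.** **1. The passages side by side**

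| Section | Route into TAU-only | Patient who fails the criteria |
|---|---|---|
| Study design | Criteria and preference | Can be TAU-only if read literally; not stated outright |
| Recruitment | Not wanting baclofen | Not mentioned |
| In- and exclusion criteria | – | Not in the study |
| Discussion | – | Not in the study (for the diseases it lists) |

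The first row and the last two cannot both hold if the first is taken at its word. Recruitment does not itself use the term eligible. That the controls are eligible patients who declined baclofen follows only from reading it together with the last two rows.

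**2. The plan's own figure**

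Inputs from Sample size calculation: 70% abstinent with baclofen, 36% without, multipliers 1.96 and 0.84, 25% dropout.

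n = (1.96 + 0.84)² × [0.70 × 0.30 + 0.36 × 0.64] / 0.34² = 7.84 × 0.4404 / 0.1156 = 29.87, so 30 per group. Then 30 / 0.75 = 40. Both stated figures reproduce. With a total of 80 in the Abstract, 40 per group is implied.

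**3. Direction**

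For the psychiatric exclusions, the Abstract's premise implies a higher relapse rate among the excluded. Counting them as controls lowers TAU abstinence and favours baclofen. For liver or renal values, pregnancy, hypertension and diabetes, the article gives no prognostic direction.

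**4. Illustration of size**

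The article gives neither the ineligible share of TAU (f) nor those patients' abstinence rate (r). Both are assumptions here. So is giving the planning rate of 36% to eligible patients who decline, because that rate comes from an earlier project whose screening the article does not describe. There is no true baclofen effect in the illustration, so the baclofen group also abstains at 36%.

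TAU rate = (1 − f) × 0.36 + f × r; spurious difference = 0.36 − TAU rate.

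The last column is the chance of a significant two-sided chi-squared result (no continuity correction), by exact binomial enumeration at 40 per group.

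| f | r | TAU rate | Spurious difference | Chance of p < 0.05 |
|---|---|---|---|---|
| 0 | – | 36% | 0 | 4.9% |
| 25% | 20% | 0.75 × 0.36 + 0.25 × 0.20 = 32% | 4 points | 6.4% |
| 25% | 10% | 0.75 × 0.36 + 0.25 × 0.10 = 29.5% | 6.5 points | 9.2% |
| 50% | 20% | 0.50 × 0.36 + 0.50 × 0.20 = 28% | 8 points | 11.6% |
| 50% | 10% | 0.50 × 0.36 + 0.50 × 0.10 = 23% | 13 points | 24.2% |

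Against the 34-point target, 4 points is 12% and 13 points is 38%. If ineligible patients did better instead (r = 46%), the bias would reverse, to −2.5 points at f = 25% and −5 points at f = 50%.

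**5. Secondary outcomes**

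Statistical analyses corrects the 3-month craving comparison for craving immediately after detoxification, and says psychiatric symptoms and quality of life are handled in a similar way. That removes part of any baseline difference in those scores. The abstinence test has no such correction.

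**The case against.** The best defence is that the Study design sentence is only loosely worded: the criteria govern entry and preference governs the arm. The other sections lean that way. The eligibility section sets conditions on the whole study, the Discussion excludes patients from the study and not from one arm, Recruitment names refusal alone, and Table 2 schedules week-0 blood and MINI-plus in both groups, which would allow common screening. The Discussion also concedes that the study is not randomized and calls it exploratory.

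Much of this stands. The benign reading is possible and may be the intended one. But then the Study design sentence says something else, and no section states that TAU-only controls are screened. The general admission about randomization does not cover the point either: the remedy it offers is matching on gender, age and pattern of GHB use, not eligibility.

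A reader might go further and infer that ineligible patients will make up much of the TAU group, so that baclofen is bound to look better than it is. The article does not support this. It gives no share of ineligible patients and never says outright what happens to a patient who fails the criteria. The direction rests on the protocol's own premise for the psychiatric exclusions only. Nor would it be right to say that craving, DASS and EQ-5D suffer as much as abstinence, given the planned baseline correction.

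**Conclusion.** The inconsistency is real and unresolved: the concurrent control group has two definitions, and one of them would confound the unadjusted 3-month abstinence comparison. If the literal reading were applied, the bias would probably favour baclofen through the psychiatric exclusions. Its sign for the somatic exclusions, and its overall size, cannot be determined from the article. The range of 4 to 13 points depends wholly on the assumed shares and rates and shows only what could happen. At its low end the effect on the false-positive rate is modest (6.4% against 4.9%). At its high end it is not (24.2%). If the criteria are in fact applied equally to both groups, this source of bias is zero, and only the wording needs correcting.

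**What to change.** Reconcile the sections before analysis.

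1. Replace the assignment sentence in Study design with wording such as: *All concurrent participants must meet the in- and exclusion criteria; among eligible patients, preference decides the group.*
2. Restrict the TAU-only comparator in the 3-month analyses to patients who meet the criteria at T0. Week-0 blood and MINI-plus, already scheduled in both groups, cover the main laboratory and psychiatric criteria. The rest, such as unstable hypertension, anticonvulsant use, Parkinson's disease and the general safety clause, need the medical record.
3. Report GHB Monitor patients who fail the criteria descriptively, outside the comparison.
4. State as a limitation that this restriction does not reach the historical controls, who are matched on age, gender, GHB use and detoxification attempts but not on psychiatric or medical status.

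The cost is one sentence, an eligibility filter and some record review. The TAU group may be somewhat smaller or fill more slowly. The change concerns only who counts as a comparator and alters no treatment rule.

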### Ethical considerations

The study was approved by the Medical Ethics Committee, Twente Medical School, Institute for Applied Scientific Research (METC/14015.kam) study number NL40321.044.13. Participants are informed about the trial and about the voluntary nature of their participation with both written and verbal communications. Participants are only included following the provision of informed consent.

### Participants

#### Recruitment

Participants are GHB dependent patients in treatment for detoxification at six participating addiction care facilities. These GHB dependent patients will be informed by their physician about the possibility to participate in the current study before GHB detoxification. The physician will inform the research nurse per centre on potential participants for the study, who will provide further study information to the patients after the detoxification. After informed consent, a research physician will perform the medical screening. The intervention group will be compared with two control groups: recently detoxified GHB dependent patients included in the Dutch national GHB Monitor 2.0, but that do not want to use baclofen (TAU only); and a matched historical control group from our previous work on GHB dependence (n = 274) of whom follow-up data are available [20]. The historical control group will be matched on age, gender, GHB use (dose and years), and number of detoxification attempts.

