#### Sample size calculation

To date, there are no published studies on the effect of baclofen on relapse in GHB dependent patients. Therefore, we used the results of previous studies on the effect of baclofen in alcohol dependent patients and our previous work on GHB dependence, in order to estimate the required sample size. Two RCTs showed that baclofen was superior to placebo in increasing abstinence rates in alcohol dependent patients: 70% (14 out of 20) versus 21% (4 out of 19) within a period of 30 days [29] and 71% (30 out of 42 p) versus 29% (14 out of 42) within a period of 12 weeks [30]. These results indicate a potential increase in abstinence of 42–49% with baclofen treatment for alcohol dependence. Results of the previous national GHB project stated that 36% of the patients succeeded to avoid relapse in GHB within a period of 3 months after detoxification without any medical interventions [20]. Therefore, we will consider a percentage of importance difference in baclofen effect in the GHB dependent participants of 34% between the Baclofen + TAU group and the TAU only or the matched control group with an expected abstinence rate with baclofen of 70% as in the alcohol studies and of 36% without baclofen.

We used the following formula comparing two proportions to calculate the sample size, n = [(Zα/2 + Zβ)^2^ × {(p1 (1-p1) + (p2 (1-p2))}] / (p1 - p2)^2^, n = [(1.96+ 0.84)^2^ × {(0.7 (1–0.7) + (0.36 (1–0.36))}] / (0.34)^2^, according to [name] sample size calculator, Exeter Initiative for Statistics. The calculation estimates that the minimal total samples size of 30 patients per group would be sufficient to detect a clinical difference of 34% in two-tailed z-test of proportions (α = 0.05, β=0.80). In the alcohol studies and our previous work with GHB inpatients an attrition rate of 13–15% was reported. We anticipate a slightly higher drop-out rate of 25%, due to the outpatient component of the baclofen treatment. Therefore we will include 40 participants in the baclofen treatment group.

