### Statistical analyses

Descriptive analysis will be executed for all measurements and will include the mean, SD and frequencies of events with confidence intervals. Descriptive statistics will be used to compare the basic characteristics of the participants in the experimental group and the control groups. To assess any difference in relapse rates between the experimental group and the control groups (TAU group and matched historical group) at 3 month after detoxification Pearson Chi-squared test will be used for the dichotomous abstinence rates. ANOVA will be carried out on continuous variables, such as the total number of abstinent days, the maximum duration of continued abstinence, time before relapse (relapse defined as ≥ 3 times GHB use per day, for 2 subsequent days), and level of substance use over a period of 3 months. At 6 months period participants who continued baclofen will be compared to those who have stopped with baclofen (after 3 month) on relapse into GHB abuse or abstinence corrected for craving. The numbers of patients maintaining abstinence will be analysed with the intention-to-treat principles. The difference in craving will be analysed by MANCOVA at 3 months between groups (abstinent experimental versus abstinent TAU or relapsed TAU) with DDQ and VAS craving as dependent variables and corrected for craving levels immediately after detoxification. The change in craving in time during the baclofen treatment will be analysed via repeated measures MANOVA. By means of MANCOVA at 6 months after detoxification the difference in craving among participants who are still using baclofen and those who have discontinued baclofen will be analysed corrected for craving after 3 months. The effect of baclofen on the psychiatric symptoms levels (DASS, MINI) and also quality of life (EQ–5D) will be analyzed similarly as for craving at 3 and 6 months. The effects of the different TAU approaches as potential confounders will be tested in a sensitivity analyses (changing one-factor-at-a-time) in an linear regression including TAU per center as covariates.

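### The historical controls appear to be selected on having follow-up data while abstinence is analysed by intention to treat, so the two sides of the 3-month comparison may rest on different populations.

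*Protocol article*

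**What the plan says.** All references are to the protocol article.

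- **Recruitment.** There are two comparators: concurrent patients who decline baclofen (TAU only), and "a matched historical control group from our previous work on GHB dependence (n = 274) of whom follow-up data are available". Matching is on age, gender, dose and years of GHB use, and number of previous detoxifications.
- **Statistical analyses.** The 3-month comparison involves both comparators: "TAU group and matched historical group) at 3 month after detoxification Pearson Chi-squared test will be used for the dichotomous abstinence rates". Later in the same paragraph: "The numbers of patients maintaining abstinence will be analysed with the intention-to-treat principles".
- **Sample size calculation.** The historical rate is given as "36% of the patients succeeded to avoid relapse in GHB within a period of 3 months after detoxification", and the planning assumption is "an expected abstinence rate with baclofen of 70% as in the alcohol studies and of 36% without baclofen". On losses: "In the alcohol studies and our previous work with GHB inpatients an attrition rate of 13–15% was reported". For the new baclofen group: "We anticipate a slightly higher drop-out rate of 25%, due to the outpatient component of the baclofen treatment".

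The article does not say whether the 274 are the whole earlier cohort or the part of it that was followed, which denominator lies behind the 36%, or how a patient without a 3-month outcome is counted.

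**The concern.** An intention-to-treat analysis counts everyone who started. A control group chosen because its outcomes are known counts only those who stayed in contact. If both descriptions are taken as written, the baclofen group is followed forward from enrolment with its losses included, and the historical group is assembled afterwards from patients who were not lost. Matching on demographic and use-history variables cannot undo selection on having an outcome.

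If loss of contact goes with relapse, the historical abstinence rate is too favourable beside an all-starters rate, and the baclofen difference comes out too small. The article intends the result to inform whether large randomised trials are warranted, so it matters that both sides of the comparison describe the same kind of population.

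**Working it through.** **Plan's own figure.** With 70% and 36%, the stated formula gives (1.96 + 0.84)² × (0.70 × 0.30 + 0.36 × 0.64) / 0.34² = 29.87, rounded up to 30 per group. With 25% drop-out, 30 / (1 − 0.25) = 40. Both figures reproduce and are not in dispute.

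**Inputs.** Control abstinence 36%, baclofen abstinence 70%, earlier attrition 13–15%, anticipated baclofen drop-out 25%, all from Sample size calculation. Two assumptions are mine: the 13–15% is loss to 3-month follow-up in the historical cohort, and lost patients relapsed.

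**Case A: 36% is the rate among followed controls.** Full-cohort rate = 0.36 × (1 − d), where d is the share lost.
- d = 0.13: 0.36 × 0.87 = 31.3%, a shift of 4.7 points.
- d = 0.15: 0.36 × 0.85 = 30.6%, a shift of 5.4 points.
- As a share of the planned 34 points: 14–16%.

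**Case B: 36% already counts lost patients as relapsed.** Followed-only rate = 0.36 / (1 − d).
- d = 0.13: 0.36 / 0.87 = 41.4%, a shift of 5.4 points.
- d = 0.15: 0.36 / 0.85 = 42.4%, a shift of 6.4 points.
- As a share of 34 points: 16–19%.

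**Effect on the difference (case A).** If baclofen drop-outs count as relapsed, the baclofen rate is 0.70 × 0.75 = 52.5%.
- Against followed-only controls: 52.5 − 36 = 16.5 points.
- Against all controls under the same rule: 52.5 − 31.3 = 21.2, or 52.5 − 30.6 = 21.9 points.
- Available cases in both groups: 70 − 36 = 34 points, with no asymmetry of this kind.

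**Dependence on what happened to lost controls (case A).** If a share q of the lost controls was abstinent, the control rate is overstated by d × (0.36 − q).

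| q | d = 0.13 | d = 0.15 |
|---|---|---|
| 0 | 4.7 points | 5.4 points |
| 0.18 | 2.3 points | 2.7 points |
| 0.36 | 0 | 0 |
| 0.50 | −1.8 points | −2.1 points |

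The sign depends on whether lost controls did worse or better than followed ones.

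**The case against.** A reader might infer that the comparison is biased against baclofen and that lost historical controls never count. The article does not support either as a settled fact, for these reasons.

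- **No missing-outcome rule is stated.** Intention to treat fixes who is analysed and in which group. It does not fix how an absent outcome is scored. The sample size keeps 70% and enrols 40 to retain 30, which looks more like planning for 30 evaluable patients than for 40 with 10 counted as relapsed.
- **Drop-out need not mean a lost outcome.** The 25% is tied to the outpatient part of treatment. Someone who stops baclofen but completes the 3-month Timeline Follow-back contributes a real outcome.
- **The 13–15% is a pooled figure.** It covers the alcohol studies and earlier inpatient GHB work, and is not shown to be 3-month follow-up loss in the historical cohort.
- **The wording about follow-up may be descriptive.** It could say that the earlier cohort was followed up, without filtering individuals.
- **The intention-to-treat sentence comes directly after the 6-month comparison within the baclofen group.** Its application to the historical test is likely, since it concerns numbers abstinent, but it is not explicit.
- **Other influences are present.** Treatment follows patient preference, and the psychological treatment of the historical group is not on record. The net direction of all biases is unknown.
- **The stakes are limited.** A concurrent TAU-only group also exists, and the article calls the study explorative. Assuming 40 per group, the standard error of the difference is √[(0.21 + 0.2304)/40] = 10.5 points, so 5 points is about half of it.

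All of this stands against an unconditional claim about direction and size. It does not remove the point. Who enters the control group is a design choice that the article itself states. It is not a detail left to an analysis plan, and on its natural reading it conflicts with an all-starters analysis.

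**Conclusion.** The concern holds in conditional form. The article appears to admit historical controls only if they have follow-up data, sets them against a group analysed by intention to treat, and does not reconcile the two.

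The understatement of roughly 5 points needs four conditions together: baclofen drop-outs scored as relapsed, lost historical controls left out, 13–15% loss in the historical cohort, and relapse among those lost. The range of 4.7–6.4 reflects the attrition range and the two readings of the 36%. If any of these conditions fails, the shift changes and may shrink, vanish or reverse. The mismatch of populations is what should be corrected, whichever way it acts.

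**What to change.** 1. Draw the matched historical controls from all detoxified patients in the earlier cohort, whether or not they were followed up. If the 274 already are that full cohort, one sentence saying so is enough. State the denominator of the 36% at the same time.
2. Apply one missing-outcome rule to the baclofen, TAU-only and historical groups, for example that a lost patient counts as not abstinent.
3. Report the followed-only comparison in all groups as a sensitivity analysis. On the planning figures, the same-rule difference (21.2–21.9 points) and the available-case difference (34 points) lie about 12–13 points apart, so readers need both.

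**Cost.** Mostly wording in Recruitment and Statistical analyses, plus some analysis work. No new patients are needed. There are two downsides. The historical abstinence rate then rests partly on an imputation rule. Matching also needs age, gender, use history and detoxification history for unfollowed patients, and the article does not confirm that these are on file. If they are not, use available cases in all groups for the historical comparison and state that limit.
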